### Primary and secondary outcomes

The primary outcome is improvement in dyspnoea, measured by a change in D-12 score between baseline and 12 months.

The secondary outcomes will be:

Proportion of participants reaching disease control or clinically important improvement as measured by disease specific questionnaires:CAT for COPD: a decrease of ≥2 points.KCCQ for heart failure: an increase of ≥5 points.CAAT for asthma: a decrease of ≥2 points.Nijmegen questionnaire for dysfunctional breathing: achieving a score ≥20.Improvement in dyspnoea, as measured by a change in D-12 score at 3 and 6 months.Time to final diagnosis.Change in mMRC dyspnoea score at 3, 6 and 12 months.Change in EQ-5D-5L at 3, 6 and 12 months.The number of hospitalisations and length of stay.Number of emergency department presentations.Change in PHQ-4 anxiety and depression score at 3, 6 and 12 months.

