**Methods and analysis:**

The BREATHE study is an open-label, cluster-randomised controlled trial of standard of care compared with a CDSS. General practices (n=40) in metropolitan, regional/rural and rural/remote settings will be recruited and randomised equally to pre-screening for chronic dyspnoea and usual standard-of-care management or pre-screening *and* CDSS-guided management. The CDSS includes an algorithm derived from a robust data and clinical knowledge model and incorporates evidence-based recommendations for the assessment and management of chronic dyspnoea. It is integrated into general practice medical software systems, fitting in the workflow of general practitioners (GPs). Eligible patients will be ≥18 years old and will have previously consented to receive SMS communication from their practice. In-scope patients will receive an automated text message prior to their GP appointment and will be screened for chronic dyspnoea (≥4 weeks). Patients identified with chronic dyspnoea will be invited to participate in the BREATHE study and followed up for 12 months. The primary outcome is improvement in the Dyspnoea-12 (D-12) score from baseline to 12 months, measured by the Dyspnoea-12 (D-12) questionnaire. Secondary outcomes include disease-specific questionnaires to assess changes in clinical outcomes, time to final diagnosis, quality of life, healthcare utilisation and costs incurred to patients.

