### Statistical analyses

The primary outcome is change in D-12 score, which has a minimum clinically important difference of 2.83 (out of a possible score of 36).^37^ Assuming a two-arm parallel cluster trial with a baseline measure, a total of 40 GP practices (clusters) provides 90% power to detect a mean difference in D-12 of four points at 0.05 significance level. To achieve this, each practice will be expected to recruit a minimum of nine participants who will be followed up for 12 months each. Allowing for a drop-out rate of 10%, we aim to recruit 10 participants per cluster for a total of 400 participants. A conservative SD of D-12 of 15 points and individual autocorrelation (the correlation between observations from the same individual at different times) of 0.65 is assumed. These calculations are robust to values of the intra-cluster correlation coefficient up to 0.10.

The primary analysis will compare change in D-12 scores at 12 months between the CDSS and standard care arms. The analysis will be performed using a repeated-measure linear mixed model including measurements taken at baseline, 3, 6 and 12 months. The model will include the effect of the visit, the randomised group and the interaction between randomised group and visit. A random cluster effect will be used to model within-cluster correlation, and a repeated effect will be used to model within-patient correlations.

A similar approach will be used to analyse secondary outcomes with logistic regression used in place of linear regression for binary outcomes. Controlled multiple imputations^38^ will be used to assess the robustness of the primary outcome results to different missing data assumptions. Sensitivity analyses including additional covariate adjustments will also be performed. A detailed statistical analysis plan will be developed and made publicly available before any analysis.

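### The four disease-specific scores (CAT, CAAT, KCCQ, Nijmegen) are listed only as responder proportions, which discards at least about a third of the information; the change in each score should be the listed outcome

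*Protocol article*

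**What the plan says.** Under Primary and secondary outcomes, the first secondary outcome is the "Proportion of participants reaching disease control or clinically important improvement as measured by disease specific questionnaires". Four cuts follow:

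- "CAT for COPD: a decrease of ≥2 points"
- "KCCQ for heart failure: an increase of ≥5 points"
- "CAAT for asthma: a decrease of ≥2 points"
- "Nijmegen questionnaire for dysfunctional breathing: achieving a score ≥20"

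The first three cut a change; the Nijmegen criterion cuts an absolute level. The same list gives D-12, mMRC, EQ-5D-5L and PHQ-4 as changes at stated visits. It does not list a change in any of the four disease-specific scores.

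Statistical analyses says: "A similar approach will be used to analyse secondary outcomes with logistic regression used in place of linear regression for binary outcomes". The Abstract describes the purpose more broadly: "Secondary outcomes include disease-specific questionnaires to assess changes in clinical outcomes".

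On collection, the Arm 2 section has the GP request these questionnaires after a provisional diagnosis is entered in the CDSS, and repeats them at follow-up. The Arm 1 section lists only mMRC, D-12, EQ-5D-5L and PHQ-4 at follow-up. Data collection describes monitoring of their completion only for CDSS practices.

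**The concern.** A responder cut treats all patients on one side of the threshold as equal. A CAT fall of 2 counts the same as a fall of 15, and a fall of 1 counts the same as a rise of 10. The full scores have to be obtained anyway to apply the cut, so the lost information is avoidable.

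The article gives no reason for handling these four instruments differently from the rest. Having a clinically important difference does not explain it: D-12 has a stated one of 2.83 points and is still analysed as a change.

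These are the trial's only disease-specific patient-reported outcomes, and each applies only to patients with one diagnosis. Precision is limited from the start, and a cruder scale makes an inconclusive result more likely.

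**Working it through.** **The plan's own figure.** The only stated power is 90% for D-12 (difference 4, SD 15, autocorrelation 0.65, 40 practices of 9, ICC up to 0.10). Take 180 per arm and a cluster autocorrelation of 1 (assumed), with DE = 1 + 8 × ICC, R = (9 × ICC + (1 − ICC) × 0.65)/DE and residual SD = 15 × √(DE × (1 − R²)).

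- ICC 0: R = 0.65, SD = 11.40, z = 4/(11.40 × √(2/180)) = 3.33. Power is 91.4% (normal) or 90.0% (t, 38 df).
- ICC 0.10: DE = 1.8, R = 0.825, SD = 11.37. Power is 91.6% or 90.2%.

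The 90% reproduces, as does 9/(1 − 0.10) = 10 per practice. No power is stated for the disease-specific outcomes.

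**Inputs for the illustration.** None is specific to CAT, CAAT, KCCQ or Nijmegen.

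- From the article, for D-12: difference 4, SD 15, autocorrelation 0.65, 9 analysed per practice, ICC up to 0.10.
- Assumed: the share f of patients with a diagnosis; scores available in equal numbers in both arms; normal change scores; a cut c of 0.15, 0.3 or 0.5 SD above the control mean change; two-sided alpha of 0.05.

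**Formulae.**

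- SD of change = 15 × √(2 × (1 − 0.65)) = 12.55, so d = 4/12.55 = 0.319.
- n = 180f per arm; m = 9f per practice; DE = 1 + (m − 1) × ICC, set to 1 if m ≤ 1; n_eff = n/DE.
- Change score: z = d/√(2/n_eff).
- Responder: p0 = P(Z > c), p1 = P(Z > c − d), z = (p1 − p0)/√((p0(1 − p0) + p1(1 − p1))/n_eff).

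**Worked case** (f = 0.40, ICC 0.05, c = 0.3). n = 72, m = 3.6, DE = 1.13, n_eff = 63.7.

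- Change: z = 1.80, power 43.6%.
- Responder: p0 = 0.382, p1 = 0.507, z = 1.44, power 30.0%.
- Relative efficiency: (1.44/1.80)² ≈ 0.64.

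**Ranges over ICC 0, 0.05 and 0.10 and the three cuts.**

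| Share f | Per arm | Power, responder | Power, change | Loss (points) |
|---|---|---|---|---|
| 5% | 9 | 8% | 10% | 2 |
| 10% | 18 | 12% | 16% | 4 |
| 15% | 27 | about 15% | 21–22% | 6 |
| 25% | 45 | 20–23% | 30–33% | 9–11 |
| 40% | 72 | 27–33% | 40–48% | 12–16 |
| 80%, pooled | 144 | 38–58% | 57–77% | 17–21 |

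Relative efficiency is 0.61 to 0.64 in every row and does not depend on sample size.

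**Other inputs.** With standardised effects of 0.3 to 0.8, 10 to 50 per arm and control responder rates of 20% to 50%, ignoring clustering, the loss runs from about 2 to 25 points. The direction is the same throughout.

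**Which rows are plausible.** The article names 22 diagnoses, and 400/22 is about 18 patients, or 9 per arm. Common diagnoses would be larger, but the article does not say by how much.

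**The case against.** **A responder proportion is a legitimate secondary outcome.** It answers directly how many patients reach a clinically important improvement, and the lack of a cited guideline is not an error. This stands, and it is why the proportions should be kept. It does not explain why the score change is left out of the list.

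**The statistical analysis plan may add score analyses.** It may: the article promises one, and it is not shown. A reader might infer that the scores will be analysed in no other way, and the article cannot support that. It does show that they are listed in no other way.

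**The power loss is not a known property of this plan.** Correct. A reader might infer a fixed loss of 6 to 19 points in small diagnostic subgroups. The inputs are borrowed or assumed, subgroups of 9 to 18 per arm lose only 2 to 4 points, and the values near 19 come from pooling 144 per arm, which is not a single-diagnosis subgroup.

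**The data are not there in both arms.** A reader might also infer that the change of analysis needs no new data. The article describes these questionnaires only in the CDSS arm. As written there is no control-arm score, so no between-arm comparison is possible in either form, and numeric analysis does not repair that. In addition, the first Arm 2 score follows the CDSS-supported provisional diagnosis, so it is not a clean baseline.

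**The practical gain is limited.** Single-diagnosis power on the change score is at most 48% in the table. This stands.

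**Conclusion.** The concern holds in a limited form. The outcome list fixes four numeric scores as responder proportions only, unlike every other questionnaire in it, and the named method for binary outcomes is logistic regression. For a roughly normal score this keeps about 61% to 64% of the information at the cuts tried, with 64% about the best possible.

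The loss of information is firm. The cost in power is illustrative. It rests on D-12 planning values, assumed cuts and diagnosis shares, and scores being available in both arms; the Nijmegen cut is on a level, so the change-score calculation carries over to it only approximately.

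The primary D-12 analysis and its 90% power are untouched. The change is worth making before analysis, but it will not make single-diagnosis comparisons well powered.

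**What to change.** 1. Under Primary and secondary outcomes, list the change in CAT, CAAT, KCCQ and Nijmegen score at 3, 6 and 12 months as the disease-specific outcome.
2. Analyse each with the linear mixed model already described under Statistical analyses, and carry this into the statistical analysis plan.
3. Keep the responder proportions as supportive results.
4. State that a between-arm comparison in either form requires the questionnaires in both arms, and reconcile the Arm 1, Arm 2 and Data collection sections on this.
5. Adjust for the first score only if it is obtained in the same way in both arms and before CDSS-guided management can affect it.

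Items 1 to 3 cost only wording. Their small downside is that a mean change is less directly interpretable than a proportion, which item 3 addresses. If the questionnaires are in fact not given in Arm 1, item 4 means extra data collection there; that is needed for the responder version too.

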#### Arm 2: pre-screening for dyspnoea and BREATHE CDSS-guided management (figure 3)

Figure 3: After obtaining consent, the participant will complete additional questions about their breathlessness and the EQ-5D-5L and the PHQ-4. Responses to all questions will be forwarded to the GP for review prior to the consultation. The GP will be directed to use the BREATHE CDSS to enter more information about the participant such as vital signs and physical examination results. This information, along with the patient responses and information extracted from the eMR, will be used in the CDSS algorithm to provide probabilities for most likely diagnoses and the most relevant diagnostic tests to perform. It is expected that the GP will use this information to inform their management, but decisions will always be at the discretion of the GP. The GP will enter their provisional diagnosis into the CDSS and if they plan to refer the participant for diagnostic tests or to a specialist. For the following provisional diagnoses, the GP will ask participants to complete the disease-specific questionnaires:

COPD Assessment Test (CAT)^31^ for participants provisionally diagnosed with COPD.Chronic Airways Assessment Test (CAAT)^32^ for participants provisionally diagnosed with asthma.Kansas City Cardiomyopathy Questionnaire (KCCQ)^33^ for participants provisionally diagnosed with heart failure.Nijmegen Questionnaire^34^ for participants provisionally diagnosed with dysfunctional breathing.

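### The Nijmegen success rule (a score of 20 or more) requires no change from the first score and, if higher scores mean more symptoms, points the wrong way

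*Protocol article*

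**What the plan says.** The section on primary and secondary outcomes introduces a family of responder outcomes as "Proportion of participants reaching disease control or clinically important improvement as measured by disease specific questionnaires". Four instrument-specific rules follow:

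- "CAT for COPD: a decrease of ≥2 points"
- "KCCQ for heart failure: an increase of ≥5 points"
- "CAAT for asthma: a decrease of ≥2 points"
- "Nijmegen questionnaire for dysfunctional breathing: achieving a score ≥20"

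The Arm 2 procedures say who completes the Nijmegen questionnaire: it is "for participants provisionally diagnosed with dysfunctional breathing". The same section repeats the relevant disease-specific questionnaires at 3, 6 and 12 months.

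The statistical analyses section covers binary secondary outcomes in one sentence: "A similar approach will be used to analyse secondary outcomes with logistic regression used in place of linear regression for binary outcomes". The article does not give the Nijmegen score range, its direction or a diagnostic cut-off, and nothing elsewhere qualifies the rule.

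**The concern.** Three of the four rules measure movement in a stated direction. The Nijmegen rule is a status with a lower bound, applied to people selected because their GP already suspects the condition. It sits under a heading about reaching control or improving, yet a participant can meet it by staying where they began.

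The second problem concerns direction. If the Nijmegen score rises with symptoms, a score at or above the cut indicates that the condition is present, and the people who recover are those who fall below it. The rule would then label the wrong side of the threshold as success.

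This is not a detail left for later. The article fixes both the threshold and the sign, so an analysis plan that followed it faithfully would code the responder indicator this way. A plan that reversed the sign without comment would contradict the published outcome.

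**Working it through.** **Inputs.** The rule, its heading and the three comparison rules come from the outcomes section; the target group comes from the Arm 2 procedures. The article gives no responder rate, first-score distribution or sample size for this outcome, so there is no plan figure to reproduce. Its power statement, "a total of 40 GP practices (clusters) provides 90% power to detect a mean difference in D-12 of four points at 0.05 significance level", concerns the primary outcome and does not enter here. All scores and rates below are assumed, for illustration.

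**Step 1: apply the printed rule to pairs of scores.** Success if the follow-up score is at least 20. The third column makes no assumption about scoring direction; the fourth assumes that higher means more symptoms.

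| First score | Follow-up score | Printed rule | Meaning if higher is worse |
|---|---|---|---|
| 30 | 30 | success | unchanged |
| 30 | 35 | success | worse |
| 30 | 22 | success | better, still above the cut |
| 15 | 25 | success | worse, has crossed the cut upwards |
| 30 | 19 | failure | better, now below the cut |
| 30 | 10 | failure | better, now below the cut |
| 15 | 10 | failure | better, below the cut throughout |

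The first row needs no premise about direction: no change counts as success. Reading the verb in the rule as a move from below 20 to 20 or more would exclude that row, but on the assumed direction it would leave only deterioration (15 to 25) as success.

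**Step 2: effect on a proportion, if higher is worse.** Let every first score be at least 20 and let a share p be below 20 at follow-up. The printed rule counts everyone else:

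reported proportion = 1 − p; error = (1 − p) − p = 1 − 2p

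| Share reaching control, p | Reported, 1 − p | Error, 1 − 2p |
|---|---|---|
| 0% | 100% | +100 points |
| 30% | 70% | +40 points |
| 40% | 60% | +20 points |
| 50% | 50% | 0 points |
| 60% | 40% | −20 points |

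At p = 50% the total happens to agree, although every participant is classified the wrong way round.

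**Step 3: is there a between-arm comparison to distort?** The Arm 1 procedures list the mMRC, D-12, EQ-5D-5L and PHQ-4. Disease-specific questionnaires appear in the Arm 2 procedures, and the data collection section describes monitoring their completion for practices in the intervention arm. As described, there is no Arm 1 Nijmegen proportion.

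Only if Arm 1 data were also obtained would the contrast change sign. With assumed control rates of 40% (standard care) and 60% (CDSS):

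- Control defined as below 20: difference 0.60 − 0.40 = +0.20; odds ratio (0.60/0.40) ÷ (0.40/0.60) = 2.25.
- Printed rule: difference 0.40 − 0.60 = −0.20; odds ratio (0.40/0.60) ÷ (0.60/0.40) = 0.44.

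**The case against.** The strongest objection is that the article never states the scoring direction. If higher meant better, the claim of reversal would fail. This stands as a limit: direction is an assumption to be confirmed, and the reversal is conditional on it.

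Next, the heading allows control as well as improvement, and an absolute threshold is a normal way to define control. That is fair, and the Nijmegen rule need not match the other three in form. But a control threshold shows that control was reached only if participants start outside it, and the rule has no such condition. For people who already have the working diagnosis, that gap matters.

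A reader might infer more than the documents support:

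- **That a beneficial CDSS would appear harmful.** This needs Nijmegen data in both arms, and the article describes them only in Arm 2.
- **That a combined disease-control proportion would be contaminated.** The article lists four instrument-specific rules and does not say that they are pooled.
- **That every success under the rule is a patient without benefit.** A participant going from 30 to 22 improves and still counts as a success.

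Finally, this may be a one-symbol slip in a condensed article, to be caught when the promised analysis plan is written. That is plausible and lowers the severity. The published definition would still need correcting, because the analysis would otherwise depart from it.

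**Conclusion.** The rule is wrong as written, within a narrow scope. Without any premise about scoring, it credits participants who start at 20 or more and do not change. On the premise that higher scores mean more symptoms, it also reverses success and failure around the cut, and the reported proportion is 1 − p in place of p when all first scores are at least 20. The numerical size depends on assumed rates, because the article gives none.

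The consequence, as data collection is described, is an Arm 2 responder proportion that cannot be read as control or improvement, for one of four instruments within a secondary outcome. A reversed treatment effect is conditional on Arm 1 data that the article does not describe. The D-12 primary outcome, its model and the sample size are unaffected. The point should be corrected before analysis, but it does not threaten the trial's main conclusion.

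**What to change.** First, confirm and state the direction in which the Nijmegen score runs. If higher means more symptoms, replace the criterion with one of these:

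- a score below 20 at follow-up among participants whose first score was 20 or more; or
- a stated decrease from the first score, in the form used for the CAT and CAAT.

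The entry condition in the first option is needed. Changing only the sign would leave the mirror-image fault: someone at 15 who stays at 15 would count as having reached control. The first option keeps the article's own value of 20; the second needs the sponsor to name and justify a size of decrease.

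Carry the corrected wording into the statistical analysis plan and the programming specification before any analysis, with a note that it replaces the published rule. The cost is one symbol and one clause, with no change to sample size, visits or data collection in Arm 2.

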### Data collection

All study data will be collected directly from the BetterConsult software of participant and GP entered information, as well as the medical information and results extracted directly from the eMR. All data will be de-identified using a 64-digit encrypted ID and uploaded into a highly secure cloud-based server housed by The George Institute for Global Health (TGI). This source data will be securely stored for 15 years. Only authorised trial staff from TGI will have access to the trial dataset. The Standard Protocol Items: Recommendations for Interventional Trials reporting guidelines were used for this protocol.^35^

All data are extracted directly from the participant, GP and practice databases and therefore considered source data, so no data monitoring is required to check for data transcription errors. There are no mandated tests or study procedures outlined in the protocol; therefore, compliance monitoring with respect to the protocol and missing data is also not required. To promote participant retention, the research team will stay in close contact with practice managers who will book the follow-up appointments for the consented patients. Data monitoring will identify upcoming and overdue visits to assist with this. Completion of the disease-specific questionnaires will also be monitored for sites randomised to the CDSS intervention arm, and if missing, the research team will contact the practice manager to follow this up with the participant.

There will be monitoring for any serious adverse events that could reasonably be considered related to study procedures. The intervention is intended solely to provide non-binding suggestions, which clinicians may choose to accept or disregard at their discretion. Therefore, clinicians retain full autonomy over all decisions regarding further investigations, management and diagnosis. The training of GPs and practice managers will cover the management of adverse events and will advise that any issues, problems or patient complaints be directed to the research team. Additionally, all participants (including practices, GPs and patients) are provided with full contact details for the relevant ethics committees in the participant information statements, should a serious adverse event or concern arise that could possibly be related to trial participation. Data monitoring for missed visits or missing data in the extraction will be conducted by the study team at TGI.

